The effectiveness of activity tracker-based interventions in everyday life could be influenced by user behavior, user satisfaction, perceived effectiveness and usefulness of the technology, and technology acceptance in general [29, 30]. Furthermore, the validity and reliability of the data collected by activity trackers could be affected by technical problems associated with the device, changes made to the device (e.g., software updates), and incorrect use of the device by the person using it or by the study personnel [31]. A systematic review conducted by Bort-Roig et al. reported that the accuracy of physical activity data (steps per day) measured with smartphones ranged from 52 to 100% [21]. Regarding the accuracy of fitness trackers, a systematic review of Fitbit devices suggested an overall tendency to underestimate steps (MD: − 9%) [32].

In previous studies in which activity trackers were used to monitor and enhance physical activity, several limitations were mentioned, including small sample sizes, short study durations, lack of standardized analytical procedures, and further research needs, such as the use of tracker interventions in subjects with T2DM [20, 26–28, 33–36]. Therefore, a RCT with a longer study duration and larger sample size relative to former studies will be conducted to investigate the effectiveness of an activity tracker-based intervention alone and in combination with a behavioral intervention. Healthy individuals, individuals with pre-diabetes and individuals with T2DM will be included in the study to assess the benefits of the intervention regarding risk reduction for the development of T2DM onset as well as disease progression. The aim of this trial is to answer the following research questions: (1) Is the use of activity trackers suitable for longitudinal assessment of physical activity in everyday life? (2) Does the use of a tracker-based intervention lead to sustainable improvements in the physical activity of healthy individuals and in people with T2DM? (3) Does the accompanying digital motivational intervention lead to sustainable improvements in physical activity for participants using the tracker-based device?

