### Objectives {7}

In this trial, it is hypothesized that the moderate and vigorous physical activity of the participants in the groups (no diabetes, diabetes and pre-diabetes) with activity tracker increases statistically significantly in terms of the target values at the 5% level of significance over time (at baseline (*t*_0_), after 3 months (*t*_1_), after 6 months (*t*_2_) and after 9 months follow-up (*t*_3_)). The measurements of moderate and vigorous physical activity with questionnaire are hypothesized to be statistically significantly different at the 5% level of significance from the measurements of physical activity with the activity tracker. In addition, an explorative hypothesis is tested: The moderate and vigorous physical activity in minutes per week measured with the activity tracker of participants in the different intervention groups (tracker-based intervention alone or tracker-based intervention combined with digital motivational intervention) increases differently over time.

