### Trial design {8}

The monocentric, pragmatic RCT has a parallel group design with an allocation ratio of 1:1. Tests of equivalence will be performed to compare the intervention group wearing a smartwatch with an activity tracker in everyday life with the control group that does not wear the device. Furthermore, 50% of the participants in the intervention group will also receive a digital motivational intervention via a smartphone app. The planning and implementation of the study is orientated towards the Declaration of Helsinki [37].

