### Outcomes {12}

The primary outcome is a change from baseline of moderate and vigorous physical activity in minutes or steps per week. Therefore, moderate and vigorous physical activity levels are aggregated and measured by one continuous variable. Physical activity is measured continuously with the tracker-based device, and algorithms are implemented to calculate amounts of different intensities [41]. Intensity levels are defined in accordance to intensity classification of Freedson et al. [48].

In addition, physical activity is assessed with questionnaires at four time points (*t*_0_, *t*_1_, *t*_2_, and *t*_3_).

As the analysis of the patient-relevant outcomes morbidity, mortality, and comorbidity of diabetes patients requires long-term studies, which are not feasible in this study due to limited project resources, the clinical outcomes HbA_1c_, body weight, and blood pressure are used as relevant surrogate parameters for these outcomes [13]. Therefore, secondary endpoints are medical parameters (HbA_1c_, TIR (time in range), BMI, and blood pressure). As covariates, psychosocial parameters (generic or diabetes-specific: health-related life satisfaction, self-efficacy, motives, volition, stages of behavioral change, personality, intention, and self-concordance), socio-demographic variables (age, gender, family background, family status, and socio-economic status), physical and mental health, comorbidities, alcohol as well as tobacco consumption, nutritional awareness, usage behavior and user satisfaction (with regard to the activity tracker and smartphone app), diabetes disease and treatment (e.g., medication), participation in external interventions, and severity of the disease are considered. The medical parameters of the healthy individuals are measured at four time points and those of the diabetes patients are collected via routine visits at the cooperating diabetes center. The data about covariates are captured with questionnaires at the same four time points. The items of the questionnaires originate from validated instruments.

In general, changes in the arithmetic means and variances of these mentioned outcomes from baseline are analyzed and compared between the intervention and control groups as well as between the four time points.

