Since comparisons between participants in the intervention and control groups as well as comparisons of participants at different time points take place, a linear mixed model with two levels will be calculated to test the primary hypotheses [78]. The dependent variable is moderate and vigorous physical activity per week measured with a questionnaire. In the linear mixed model, time (*t*_0_ to *t*_3_) is the intra-class factor, and grouping (intervention group with tracker-based device, intervention group with tracker-based device and digital behavior intervention, and control group) is the inter-class factor [78]. The covariates psychosocial factors, socio-demographic factors, physical and mental health, comorbidities, alcohol and tobacco consumption, nutritional awareness, usage behavior and user satisfaction (with regard to the activity tracker and app), diabetes disease and treatment, participation in external interventions, and severity of the disease are assessed as categorical variables. Random intercepts are assumed while all other effects are regarded as fixed. The null model will be calculated and compared with alternative models regarding its fit via Akaike and Bayesian information criterion [78, 79]. Further, interactions will be considered and will be included in the model if the explanatory power of the model is strengthened. The same analysis will be performed for the assessment of secondary endpoints. Effects of all analyses will be considered significant if *p* < 0.05. All assumptions of the statistical tests will be checked in advance graphically and by appropriate tests. Bonferroni correction will be applied to counteract the problem of multiple testing [80].

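### The primary analysis does not say which arm contrast and which visit answers research question 2, and the promised Bonferroni correction has no stated family

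*Protocol article*

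**What the plan says.** Research question 2, in Background and rationale {6a}, reads "Does the use of a tracker-based intervention lead to sustainable improvements in the physical activity of healthy individuals and in people with T2DM". It names no arm pair and no visit.

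Four sections of the protocol then describe the comparison differently:

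- **Objectives {7}**: activity in the tracker groups "increases statistically significantly in terms of the target values at the 5% level of significance over time". Control is not mentioned. Only the comparison of the two tracker arms is set apart as exploratory ("In addition, an explorative hypothesis is tested"), namely that their activity "increases differently over time".
- **Trial design {8}**: "The monocentric, pragmatic RCT has a parallel group design with an allocation ratio of 1:1". The plan is to "compare the intervention group wearing a smartwatch with an activity tracker in everyday life with the control group", and the same sentence announces equivalence testing for this purpose. Half of the intervention group also receives the motivational intervention.
- **Outcomes {12}**: changes from baseline are "compared between the intervention and control groups as well as between the four time points".
- **Statistical methods {20a}**: a two-level linear mixed model of questionnaire activity tests the primary hypotheses. Time runs from t0 to t3, and "grouping (intervention group with tracker-based device, intervention group with tracker-based device and digital behavior intervention, and control group) is the inter-class factor". Interactions enter only if they add explanatory power. Every analysis uses p<0.05, and a Bonferroni correction is promised without naming the tests it covers.

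The only visit singled out in {20a} is t2, and only for the Bland-Altman comparison of tracker and questionnaire.

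**The concern.** A three-arm factor crossed with time does not yield one answer until someone chooses a contrast. For research question 2 the choices are tracker alone, tracker plus motivational intervention, or both pooled, each against control, at t1, t2 or t3. A single omnibus group-by-time test is another option, but the protocol does not name it, and the term it needs enters the model only conditionally.

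These choices answer different questions. Pooling dilutes an effect confined to one arm, and splitting loses precision if both arms work. t1 and t2 fall within the six months of tracker use, whereas wearing is optional between t2 and t3, so t2 and t3 carry different meanings of a sustainable effect.

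If the choice is left until the data are seen, the result reported as primary can depend on it. The actual error rate then depends on a Bonferroni family that is also undefined.

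**Working it through.** **1. The plan's sample size does not reveal the contrast.** Sample size {14} gives d=0.5, f²=0.15, power 0.8, α=0.05, correlation 0.33, 15% drop-out, an unquantified design effect, and N=1642.

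- Two-group comparison at d=0.5: 63 per arm, 126 in total.
- Regression with f²=0.15: 55 to 98 in total for 1 to 6 tested predictors.
- Assumed design effect 1+(4−1)×0.33 = 1.99. Then 55×1.99/0.85 ≈ 129 and 126×1.99/0.85 ≈ 295.
- Reaching 1642 from these bases needs a design effect between 1642×0.85/126 ≈ 11 and 1642×0.85/55 ≈ 25.

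The figure is not reproduced. Without the design effect and the number of predictors it cannot be checked, so it does not show which contrast was powered.

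**2. Inputs for the contrasts.** Completers: 1642×0.85 ≈ 1395, so about 698 control and 349 in each tracker arm. The simulation used 697, 348 and 348. Assumed: two-sided 0.05, unit SD at each visit, equal correlation r=0.33 between visits, change from baseline, no clustering.

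**3. Correlations.**

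- Same contrast at two visits: (1−r)/[2(1−r)] = 0.5.
- The two single-arm contrasts: (1/698)/(3/698) = 0.33.
- Pooled with either single-arm contrast: 2/√(2×3) = 0.82.

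**4. False positives with no true effect** (400,000 simulated trials):

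| Rule | At least one false positive |
|---|---|
| Pooled, 3 visits, uncorrected | 12.6% |
| Two single-arm contrasts × 3 visits, uncorrected | 22.8% |
| All nine, uncorrected | 24.7% |
| All nine, each tested at 0.05/3 | 9.6% |
| All nine, each tested at 0.05/6 | 5.2% |
| All nine, each tested at 0.05/9 | 3.6% |

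If the family is three and only the three pooled contrasts can decide, the rate is 4.4%. The 9.6% arises when the correction counts three tests but the reading ranges over nine.

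**5. Power.** 80% power corresponds to a standardized signal of 1.960+0.842 = 2.802.

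- The variance ratio of single-arm to pooled contrast is (1/349+1/698)/(2/698) = 1.5. An effect with 80% power pooled therefore has Φ(2.802/√1.5−1.960) = Φ(0.33) ≈ 63% in one arm.
- Bonferroni over nine has critical value 2.773, giving Φ(2.802−2.773) ≈ 51%.
- The effect behind these figures is d = 2.802×√(2×0.67)×√(2/698) ≈ 0.17 for the pooled contrast.

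**6. Do the nine disagree?** Uncorrected tests, assumed effects:

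| Effects (SD units) | Result |
|---|---|
| 0.5, both arms, all visits | all nine agree in practically every trial |
| 0.2, both arms, all visits | some significant, some not, in 66% |
| 0.1 tracker alone, 0.3 with motivational intervention | pooled significant at t2, tracker alone not, in 64% |
| 0.3 at t1 and t2, 0.1 at t3, both arms | pooled significant at t2, not at t3, in 63% |

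**The case against.** **The pooled and three-arm descriptions are compatible.** This stands. The split is nested: tracker versus control 1:1, then half the tracker group gets the added intervention. The section on comparators {6b} explains why, and the pooled comparison is a linear combination of the three-level factor. A reader might infer an outright contradiction, but the documents do not support that. What is missing is a statement that this combination, or another, decides.

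**Bonferroni is promised.** This also stands. A reader might take 25% as the trial's error rate, but that ignores the stated correction. With a family of nine the rate is below 5%. The correction still does not say which contrast gives the answer, and its strength depends on the family.

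**The count could be pushed to twelve** by adding the comparison of the two tracker arms. Objectives {7} labels that comparison exploratory and it belongs to research question 3, so it is not counted here.

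**At the planning effect the choice is immaterial.** This is true for d=0.5 in both arms at all visits. Even d=0.5 confined to the combined arm leaves a pooled effect of 0.25 and about 98% power. But Background {6a} cites standardized differences of 0.20 for steps and 0.17 for moderate to vigorous activity with wearables alone, which is the range where the choice matters.

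**The hypothesis is framed over time, which fits one omnibus test.** It does, but no such test is named and its interaction term is not guaranteed.

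**This is detail for the analysis plan.** A gatekeeping order could be left there. The protocol's own sections, however, describe a within-group increase, an equivalence test and a three-arm model for the same question, and these need reconciling in the protocol.

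**Conclusion.** The point holds in this form: the protocol names no arm contrast and visit, and no omnibus test, that decides research question 2, and its descriptions of the primary comparison in {7}, {8}, {12} and {20a} do not converge on one. Error across the nine arm-by-visit contrasts is about 3.6% to 9.6%, depending on whether the unstated Bonferroni family is nine or three. About 25% applies only if no correction is made.

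The power figures (80% falling to 63% in one arm, or to 51% under Bonferroni over nine) and the disagreement rates of 63% to 66% are conditional on small, unequal or fading effects. They do not hold at a uniform d=0.5. They also rest on about 1395 completers, equal correlation between visits and no clustering. It should not be inferred that the trial would generally give contradictory answers, or that 1642 is wrong; the latter is only uncheckable.

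This should be corrected before analysis, but it does not undermine the design.

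**What to change.** In Statistical methods {20a}, name one primary contrast. For example: the difference between both tracker arms pooled and control in change from baseline in questionnaire-measured moderate and vigorous activity (minutes per week) at one stated visit, as a two-sided test of difference at 0.05. Estimate it as a linear combination (weights ½, ½, −1) from the three-level group-by-time model, and keep the interaction in the model whatever the fit criteria say.

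Place the remaining arm and visit contrasts either in a stated fixed order or in a Bonferroni family with its number of tests given. The sponsor should choose the visit and the order according to what sustainable is meant to claim. Keep the comparison of the two tracker arms exploratory. Then align Objectives {7}, which has no control contrast, and Trial design {8}, which speaks of equivalence, with the chosen contrast, and state in Sample size {14} that this is the contrast powered.

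Under the assumptions above, a single pooled contrast has type I error 5% and power 0.36, 0.68 and 0.90 at d=0.1, 0.15 and 0.2. With Bonferroni over nine, power at d=0.2 would be 0.67.

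The cost is wording only, with no added data or participants. The downside is that contrasts outside the primary one, or late in the order, can no longer be claimed on their own.

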### Relevant concomitant care permitted or prohibited during the trial {11d}

Because it is not possible to prevent participants from taking part in classes or other interventions that promote a healthy lifestyle, the participation in such interventions is queried at each measurement point and the results of the statistical analyses will be adjusted for such effects if necessary.

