### Participant timeline {13}

Participants who give their informed consent and fulfill the inclusion criteria are assessed at four timepoints (see Table 1 and Fig. 1). At baseline, a questionnaire with socio-demographic questions [51] is administered, and at all four time points, a questionnaire with health-related questions [52], questions regarding physical activity [53, 54], a psychosocial questionnaire [55–64], and questions regarding the use of tracker-based devices and apps outside this study is administered. In addition, the diabetes parameters are measured in a standardized way by qualified study personnel at all four time points. Questions regarding the usability of and satisfaction with the app and the tracker-based device [65] are asked after 6 months and regarding the follow-up use of the device after 9 months.

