**Fig. 1 Fig1:**
[figure not shown]
Graphical representation of the study design according to Consolidated Standards of Reporting Trials (CONSORT, [49, 50])

At baseline, participants are randomly assigned to either the intervention or the control group. For participants in the intervention group wearing the tracker-based device, physical activity is measured continuously with the device for 6 months. For the remaining 3 months, participants can decide on their own if they want to continue wearing the tracker until t_3_. At t_3_ they have to return the tracker to the study personnel.

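### The between-arm primary model lists covariates measured after randomisation, one of which (satisfaction with the study tracker and app) cannot exist in the control group

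*Protocol article*

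**What the plan says.** All references are to the protocol article.

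- Statistical methods {20a} states that "a linear mixed model with two levels will be calculated to test the primary hypotheses". The arms compared are control, tracker alone, and tracker plus digital motivational intervention, over t0 to t3. The covariates include psychosocial factors and "usage behavior and user satisfaction (with regard to the activity tracker and app), diabetes disease and treatment, participation in external interventions". On their status: "Random intercepts are assumed while all other effects are regarded as fixed". On selection: "The null model will be calculated and compared with alternative models regarding its fit via Akaike and Bayesian information criterion". The secondary endpoints get the same analysis.
- Outcomes {12}: "The data about covariates are captured with questionnaires at the same four time points".
- Participant timeline {13}: "Questions regarding the usability of and satisfaction with the app and the tracker-based device [65] are asked after 6 months". The same section has use of trackers and apps outside the study asked at all four visits.
- The text under Fig. 1: "At baseline, participants are randomly assigned to either the intervention or the control group". Three of the four covariate measurements therefore follow randomisation.
- Relevant concomitant care {11d}: participation in other lifestyle programmes is asked at every visit, and "the results of the statistical analyses will be adjusted for such effects if necessary".
- The Abstract and Trial design {8} give the control group no intervention and no device. The Discussion says that psychological factors will be controlled for. Section {20c} states an intention-to-treat analysis.

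**The concern.** A randomised comparison keeps its causal meaning when the model adjusts only for variables fixed before allocation. The listed set breaks this in two ways.

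First, satisfaction with the study tracker and app, and usage of them, are defined only for people who were given them. As covariates in a model that includes controls, they overlap with the group factor itself.

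Second, psychosocial variables such as self-efficacy, volition and intention, and attendance at other programmes, can themselves be changed by a motivational intervention. Adjusting for their later values removes whatever part of the effect runs through them.

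Every contrast with control, for primary and secondary endpoints, runs through this model.

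**Working it through.** The plan gives no figure of its own on this point, so there is none to reproduce. The sample size of 1642 serves only to set arm sizes: 1642 / 2 = 821 controls, with the other 821 split into 411 and 410.

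**1. When and in whom the tracker/app covariates exist.** {12} places all covariates at four visits; {13} places satisfaction and usability after 6 months only. These two statements need aligning. No baseline value of satisfaction can exist. Controls have no study device under the Abstract, {8}, {6b} and {18a}. Section {11c} speaks of control participants being told to wear the device, which conflicts with those sections and must be reconciled.

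**2. Estimability.** Fixed-effect columns: intercept 1, group 2, time 3, group-by-time 6, and satisfaction 3 (assumed levels 1 to 3, with a not-applicable reference for controls). Total: 1 + 2 + 3 + 6 + 3 = 15.

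| Handling of satisfaction | Linear dependence | Rank | Consequence |
|---|---|---|---|
| Constant per person | sum of 3 satisfaction columns = sum of 2 group columns | 14 of 15 | group main effects against control not estimable; group-by-time estimable |
| Entered at t2 only | sum of 3 satisfaction columns = sum of 2 group-by-t2 columns | 14 of 15 | group-by-t2 against control not estimable; group-by-t3 estimable |
| Complete cases | no control has a value | – | 0 of 821 × 4 = 3284 control rows remain; no contrast with control estimable |

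In the first case the surviving group-by-time terms are still conditioned on something measured after randomisation.

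**3. Covariates that exist in all arms.** If part of the effect is carried by a covariate, and nothing unmeasured affects both covariate and outcome, then adjusted effect = total × (1 − share mediated). The document gives no share, so a range is shown. Take the total as 0.50, the d assumed in Sample size {14}:

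- 25%: 0.50 × 0.75 = 0.375
- 50%: 0.50 × 0.50 = 0.25
- 75%: 0.50 × 0.25 = 0.125

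A simulation of one follow-up visit used 400 runs, arms of 821/411/410, the same effect in both tracker arms, and a mediator shifted by 0.6 SD. The mediator was entered in five categories because {20a} treats covariates as categorical.

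| Share mediated | Unadjusted | Adjusted | Adjusted, with an unmeasured common cause |
|---|---|---|---|
| 25% | 0.505 | 0.393 | 0.340 |
| 50% | 0.498 | 0.273 | 0.231 |
| 75% | 0.501 | 0.162 | 0.121 |

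Without the mediator the model recovers 0.50. With it, the estimate drops to about 0.39, 0.27 and 0.16. Where an unmeasured factor drives both mediator and outcome, it can fall below the direct effect (0.340 against 0.375, for example).

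**4. Selection by fit.** The Akaike and Bayesian criteria reward variables that predict activity. A strong mediator does so, and tends to be kept.

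**The case against.** The strongest reply is that the article does not fix full adjustment for later values. It lists the covariates without saying which visit's values enter, {11d} adjusts only where needed, and model comparison may drop terms. An analysis plan could specify t0 values, and then no mediator bias would arise. This stands for the psychosocial factors: the attenuation is conditional, the mediated share is assumed, and some of these items, such as personality, are unlikely mediators. It does not help satisfaction with the study device, which has no t0 value to use.

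Four stronger readings are tempting, and the documents do not support them.

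- *The randomised effect cannot be estimated at all.* This depends on a coding that the article does not state. With satisfaction constant per person, all six group-by-time terms remain estimable. (That presupposes the interaction is in the model, which {20a} leaves to explanatory power.)
- *All controls will be deleted.* That is a complete-case scenario, and it would contradict the intention-to-treat rule in {20c}.
- *Usage as well as satisfaction is asked only at 6 months.* {13} ties only usability and satisfaction to that visit. Outside-study tracker and app use is asked at all four visits with no restriction by arm, so part of usage behaviour can exist in controls and at baseline.
- *The model would estimate exactly the direct effect.* That holds only without unmeasured causes shared by mediator and outcome.

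**Conclusion.** The covariate list in {20a} is wrong as written. It places study-tracker and app satisfaction and usage in a comparison with people who have neither, and it leaves psychosocial factors and external-programme participation unrestricted to baseline. The first part follows from the text alone. Its consequence ranges from contrasts with control that are not estimable to group-by-time contrasts that are estimable but conditioned on a post-randomisation variable, depending on coding.

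The second part is conditional on t1 to t3 values entering. If they do, the target is no longer the total intention-to-treat effect, and the estimate shrinks to the extent that these variables mediate it. The figures of 0.39, 0.27 and 0.16 illustrate that; they are not predictions. Socio-demographic covariates, asked at baseline only, are unaffected. Entering continuous covariates as categories is a secondary matter of precision. The point should be settled before analysis, since all contrasts with control depend on it.

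**What to change.** In {20a}, limit the effectiveness model to group, time, group-by-time, the stratification factor in {16a} (no disease, pre-diabetes, diabetes) and a short prespecified list of t0 covariates, with continuous ones preferably kept continuous.

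State how baseline activity is handled. The model already has t0 as a response, so either keep it there or remove the t0 rows and use it as a covariate, not both. With the stated correlation of 0.33, the variance factor for change from baseline is 2 × (1 − 0.33) = 1.34. For baseline as covariate it is 1 − 0.33² = 0.891. The standard-error ratio is √(0.891 / 1.34) = 0.82. That gain does not appear if baseline is added as a covariate while the t0 rows stay.

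Remove from this model study-tracker and app usage and satisfaction, external-programme participation after randomisation, and psychosocial values from t1 to t3. Move them to labelled exploratory adherence or mediation analyses, with tracker and app variables analysed within the tracker arms only. Align {11d} with this, and correct {12} so that its timing of covariates agrees with {13}.

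The cost is wording; no new data are needed. The one downside is that results adjusted for these variables become exploratory.

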Socio-demographic and socio-economic factors are measured with standardized indicators of the German Federal Statistical Office [51, 71, 72]. The health-related questions are based on the questionnaire used in the Robert Koch Institute’s German Health Update (GEDA) survey, which includes indicators of the European Health Interview Survey [52]. Therefore, data based on these indicators are comparable with the results of other national and international surveys [73]. Physical activity is measured with the tracker-based device in the intervention group and the Questionnaire for Motor Skills (FFB-mot, [53]) as well as the Movement and Sport Activity Questionnaire (BSA-F, [54]) in the intervention and control group to enable comparison of the different measurements. Both FFB-mot and BSA-F have acceptable psychometric properties [53, 54]. The psychosocial questions are based on questionnaires assessing sport and exercise-related self-efficacy [55, 56], sport and exercise-related volition (Volition in Exercise Questionnaire - VEQ, [57]), behavior change motivation [58], motives and goals with regard to sport and exercise (Bernese Motive and Goal Inventory - BMZI, [59]), affect towards sport and exercise as adapted by Brand [60] from Crites et al. [74], barriers for physical activity as assessed in Brehm et al. [61], and the intention to be physically active [62], as well as the Big Five Inventory (BFI-10, [63]) to assess the subjects’ personality and the Short Scale for Measuring General Self-efficacy Beliefs (ASKU, [64]) to assess the subjects’ general self-efficacy. User satisfaction as well as usability related to the tracker-based device and app are measured with a translated and modified version of the patient version of the mHealth App Usability Questionnaire (MAUQ), which has been shown to be valid and reliable (Cronbach alpha=0.914) [65]. The wearable device (Bangle.js) is also rated by the subjects with a translated version of the Comfort Rating Scale (CRS) by Knight and Baber [75].

The questionnaires are administered on an internet platform for practicability and accuracy reasons.

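### Coding every covariate of the primary mixed model as categorical, age and psychosocial scores included, costs the arm main effect a little precision and adds arbitrary class boundaries, with no reason given

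*Protocol article*

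**What the plan says.** Section {20a} specifies a two-level linear mixed model with time and group as factors. Its covariate sentence opens with "The covariates psychosocial factors, socio-demographic factors, physical and mental health, comorbidities" and ends by stating that "participation in external interventions, and severity of the disease are assessed as categorical variables". The statement covers the whole list, and no covariate is exempted.

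Two other sections show what the list contains. Outcomes {12} names "socio-demographic variables (age, gender, family background, family status, and socio-economic status" as the socio-demographic covariates, so age is one of them. Plans for assessment and collection of outcomes {18a} takes the psychosocial covariates from multi-item instruments, for example the "Short Scale for Measuring General Self-efficacy Beliefs (ASKU, [64]) to assess the subjects’ general self-efficacy", along with inventories of volition, motives and personality.

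Three further statements bear on the consequences:
- On timing, {12} says "The data about covariates are captured with questionnaires at the same four time points".
- On random effects, {20a} says "Random intercepts are assumed while all other effects are regarded as fixed".
- On interactions, {20a} says "Further, interactions will be considered and will be included in the model if the explanatory power of the model is strengthened".

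Section {20a} also compares the null model with alternatives by AIC and BIC, and applies the same analysis to the secondary endpoints.

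**The concern.** Age is a continuous quantity, and a multi-item scale normally yields an ordinal or near-continuous score. Cutting such a variable into classes makes the model assume the same expected activity for everyone in a class and a jump at each boundary. With k classes it spends k − 1 parameters where a linear term spends one.

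Two things are at stake. The first is precision: less between-person variation in activity is explained, so an arm effect averaged over visits has a wider interval than the collected data allow. The second is arbitrariness: neither the number of classes nor the boundaries are given, yet both affect the fit and the parameter count on which AIC and BIC compare models. The same rule carries over to HbA1c, time in range, BMI and blood pressure.

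The point concerns only the coding of the covariates. Which covariates, or which of their time points, should be adjusted for is a different question.

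**Working it through.** The plan gives no figure for covariate strength or coding, and its sample size section describes no covariate adjustment. There is therefore no figure of the plan's own to reproduce on this point.

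**Inputs**
- Correlation between measurement times 0.33, from Sample size {14}. With a random intercept and total variance 1, between-person variance is 0.33 and within-person variance is 0.67.
- Four visits (t0 to t3) and dropout of 15%, from the protocol.
- Assumed: one normally distributed, time-constant score with a linear effect, cut into equal-sized classes, explaining a share R of between-person variance, with R from 10% to 50%.

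**Step 1. Share e of the score's explained variance that survives the cut.** For a normal score, e is the variance of the class means. Two classes give 2/π = 0.637, three give 0.793, four give 0.861 and five give 0.897.

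**Step 2. Arm main effect, complete data.** Its variance is proportional to the residual variance of a person's four-visit mean:
- continuous: 0.33(1 − R) + 0.67/4
- categorised: 0.33(1 − eR) + 0.67/4

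Arm sizes cancel in the ratio. At R = 0.10 the continuous value is 0.297 + 0.1675 = 0.4645. The median split gives 0.3090 + 0.1675 = 0.4765, a ratio of 1.026. At R = 0.50 the values are 0.165 + 0.1675 = 0.3325 and 0.2250 + 0.1675 = 0.3925, a ratio of 1.180.

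| R | Median split | Tertiles | Quartiles |
|---|---|---|---|
| 10% | 1.026 | 1.015 | 1.010 |
| 20% | 1.056 | 1.032 | 1.021 |
| 30% | 1.090 | 1.051 | 1.035 |
| 50% | 1.180 | 1.103 | 1.069 |

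Interval width follows the square root: about 1% to 9% wider with a median split (√1.026 = 1.013, √1.180 = 1.086), and 0.5% to 3% with quartiles (√1.010 = 1.005, √1.069 = 1.034).

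**Step 3. Group-by-time contrast.** With complete data, a person's change between two visits has variance 2 × 0.67 = 1.34. Between-person variance cancels, so the ratio is 1.000 however a time-constant covariate is coded. With 15% dropping out after one to three visits, generalised least squares gives a median-split ratio of 1.0007 at R = 20% and 1.0022 at R = 50%. The corresponding main-effect ratios are 1.054 and 1.174, close to the complete-data values.

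Scores that change between visits could also affect within-person variance. The documents give nothing from which to size that.

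**The case against.** **The trial targets change, not an averaged level.** The primary outcome in {12} is change from baseline, and Objectives {7} hypothesises an increase over time. Step 3 shows that a group-by-time contrast hardly notices the coding of a time-constant covariate. This stands, and it removes most of the practical weight. A reader might infer that the trial's main contrast is compromised; the documents do not support that. The arm main effect matters only because {20a} makes interactions conditional on model improvement. If it were reported, averaging in the pre-intervention visit would be a larger and separate fault.

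**A power gain cannot be claimed.** A reader might infer that continuous coding lifts the planned 80% power by several points. That needs a median split, which the plan never mentions, and strong covariates: 15% of single-visit variance is 0.15/0.33, or about 45% of all between-person variance. Nor is 80% a firm starting point. The stated d = 0.5 needs 126 participants, or 126 × 1.99/0.85 ≈ 295 with an assumed design effect of 1 + 3 × 0.33 = 1.99 and 15% dropout. At about 1642 × 0.85 ≈ 1396 completers, power at d = 0.5 already exceeds 0.9999.

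**Categories have a use.** They capture non-linearity without an assumed form, and splines also cost parameters. So it would be too strong to say that categorising brings no gain. The plan does not offer this reason, however, and a spline achieves it without discarding information within classes.

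**The wording is open.** The sentence could mean that variables are collected in classes; Data management {19} prefers closed-ended fields, and {18a} states no scoring. Much of the list is naturally categorical. But the sentence sits within the model specification, so the variables would still enter as classes. Detailed coding may be left to a SAP, but here the article itself fixes a rule.

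**Conclusion.** The point holds as a minor efficiency matter. Section {20a} prescribes categorical coding for the whole covariate list, including age and psychosocial scales, without a reason or exception. That discards information and adds unspecified boundaries to a model compared by AIC and BIC.

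The variance of the arm main effect rises by about 1% to 7% with quartiles and 3% to 18% with a median split. These ranges rest on an assumed covariate strength of 10% to 50% of between-person variance, a normal score with a linear effect, and equal-sized classes. The documents supply neither the covariate strength nor the number of classes, so the true loss cannot be derived from them. That age and the scales yield continuous or ordinal values follows from what they are; the article does not state the scoring.

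A reader might also infer that the treatment comparison is biased. It is not: the coding of covariates leaves the randomised comparison unbiased.

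**What to change.** In {20a}, replace the statement on categorical coding by:

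*Covariates recorded on a continuous or multi-item score scale (e.g. age, psychosocial scale scores) enter the model as continuous terms, linear or with a spline where the graphical check shows non-linearity; only naturally categorical covariates, or those collected only in bands, enter as categories.*

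The text deliberately does not restrict scores to baseline values. Covariates are collected at four time points, and satisfaction with the device and app is first asked after 6 months (Participant timeline {13}), so it has no baseline value. The change alters only how covariates are coded.

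The cost is one sentence and no new data, since anything collected only in bands stays categorical. It adds a linearity check, which fits the graphical assumption checks already planned in {20a}, and a few parameters where splines are used.
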